### Mode of Stimulation

Group classification based on the mode of stimulation is listed as follows:

Group 1: PlaceboGroup 2: High-frequency rTMSGroup 3: iTBS

### Site of Stimulation

Group classification based on the site of stimulation is listed as follows:

Group 3: iTBS on motor cortexGroup 4: iTBS on the SCGroup 5: iTBS on the motor cortex and SC

This trial’s conduct and report will follow the CONSORT (Consolidated Standards of Reporting Trials) statement for randomized trials (Figure 1).

**Figure 1 figure1:**
[figure not shown]
CONSORT (Consolidated Standards of Reporting Trials) flow diagram. ASIA: American Spinal Injury Association; BDI: beck depression inventory; cSP: cortical silent period; ICF: intracortical facilitation; iTBS: intermittent theta burst stimulation; LICI: long-interval intracortical inhibition; MAS: ___; MC: motor cortex; MEP: motor evoked potential; QOL: quality of life; rTMS: repetitive transcranial magnetic stimulation; SC: spinal cord; SCIM: Spinal Cord Independence Measure; SICI: short-interval intracortical inhibition; STAI: State-Trait Anxiety Inventory; VAS: Visual Analog Scale.

### Patient Recruitment and Parameter Recording

Participants will be enrolled from the Jai Prakash Narayan Apex Trauma Centre at AIIMS (All India Institute Of Medical Sciences) Delhi. Following SCI surgery, a 15-day period will be designated for vertebral stabilization, after which sutures will be removed on the 15th day. Once the sutures are removed, baseline parameters will be measured. Patients will then be randomly assigned to one of the intervention groups. After completing the intervention, postintervention parameters will be recorded and follow-up assessments will be conducted at 1, 2, and 3 months (Figure 2). To ensure consistency during the intervention, all assessments will be recorded by the blinded primary investigator.

**Figure 2 figure2:**
[figure not shown]
Timeline: all the intervention and recording paradigms are organized as a timeline. iTBS: intermittent theta burst stimulation; rTMS: repetitive transcranial magnetic stimulation.

### Intervention Protocol

During the intervention phase, patients will be randomly allocated to one of the interventional groups. The rTMS or iTBS will be administered using the Neurosoft - Neuro-MS 5 device (Neurosoft Ltd), a commercially available transcranial magnetic stimulator. The device will be equipped with both an angulated figure 8–shaped coil and a circular coil for stimulation. The intervention (rTMS or iTBS) will be applied to the lower-limb motor area located in M1 (to stimulate both lower limbs), with the handle of the coil aligned parallel to the interhemispheric midline (pointing occipitally) based on the vertex position according to the International 10-20 EEG system. For SC stimulation, the circular coil will be positioned over the injury site. In the placebo stimulation group, a sham coil (not generating a magnetic field but producing similar click sounds) will be used and the stimulation protocol remains akin to the iTBS group.

The standard protocol for iTBS will be used: 3-pulse bursts at 50 Hz, repeated at 5 Hz, with a 2-second train repeated every 10 seconds for 20 repetitions, amounting to a total of 600 pulses [7]. The rTMS protocol will consist of 1600 pulses at a frequency of 20 Hz, with a 2-second train repeated every 30 seconds for 20 minutes [9]. A resting motor threshold (RMT) of 90% will be used for both rTMS and iTBS stimulation intensity. RMT will be determined by recording MEP from the abductor pollicis brevis (APB). RMT will be recorded by placing figure-eight coils over the motor hotspots of the APB. The minimum stimulus intensity that causes an MEP with a peak-to-peak amplitude of at least 50 µV in at least 50% of consecutive stimuli will be considered as RMT. Interventions will be administered for 5 consecutive days, twice daily, with a total of 10 sessions [10].

### Postintervention Care

All the participants will be required to fill out a TMS safety questionnaire both before and after the intervention. Briefly, the preintervention questionnaire takes care of any implants, past history of seizures, pregnancy, or head trauma, whereas the postintervention questionnaire reports any adverse effects observed by patients like headache, nausea, ear discomfort, or any seizure. Besides these, the participants will also undergo thorough screening for contraindications, continuous monitoring during and after stimulation, and adherence to standardized emergency protocols as approved by the institutional review board. If a patient experiences an adverse event during the trial, the principal investigator will provide treatment and corresponding financial compensation. Patients who are enrolled in the placebo group will also receive the conventional rehabilitation program during the study.

### Outcomes

#### Primary Outcome (Neurological)

The primary outcome will measure the severity of injury with the ASIA Scoring System. The ASIA impairment score (AIS) ranges from complete loss of sensation and movement (AIS=A) to normal neurological function (AIS=E). The ASIA motor score uses a test of the strength of 10 key muscles on each side of the body (eg, elbow flexors, wrist extensors, hip flexors, quadriceps, and dorsi flexors). The score ranges from 0 (no contraction) to 5 (normal resistance) through a full range of motion. A total possible score of 50 for the upper extremities and 50 for the lower extremities may be obtained [11]. The ASIA sensory score involves pinprick and light touch sensation at key points representing each dermatome of the body, scored on a 3-point scale (0, 1, and 2). Scores are summed to give a total possible score of 224, where a higher score indicates better sensation than a lower score.

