### Inclusion and Exclusion Criteria

Adults aged 18 to 60 years with a thoracolumbar (T1-L5) SCI and complete motor loss below the lesion level (American Spinal Injury Association [ASIA] score A) will be screened and recruited within 1 month of injury.

Exclusion criteria include patients with osteoporotic fractures, a history of neurological or orthopedic diseases affecting the SC, head injuries, ferromagnetic metallic implants near the target stimulation area, pacemakers, cognitive impairment, pregnancy, a history of seizures, or acute eczema or bedsores.

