#### Statistical Analysis

Data will be analyzed using STATA 14.0 software (StataCorp). Continuous variables will be presented as mean and SD, and categorical variables as frequencies and percentages. The primary analysis will be the intention-to-treat analysis, where baseline values will be carried forward for subjects with missing data. Unless stated otherwise, intention-to-treat data will be presented throughout the study. In addition, a per-protocol analysis will be conducted, including only participants who comply with the protocol.

Normality will be evaluated using the Shapiro-Wilk test for each outcome, homogeneity of variance will be checked using the Levene test, and the Mauchly test will be used for sphericity. Depending on the data distribution, parametric or nonparametric tests will be applied.

If the data are found to be uniformly distributed, we will use repeated measures ANOVA to assess changes over time within and between groups. Bonferroni or Tukey correction will be done for post hoc pairwise comparisons. Nonparametric tests like the Friedman test followed by appropriate post hoc tests will be used for skewed data. Corrections for multiple comparisons will be applied as specified to reduce the risk of type I errors. To analyze categorical variables, the chi-square or Fisher exact test will be used to assess associations between groups.

A *P* value less than .05 with a 95% CI will be considered statistically significant.

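### The primary outcome is named only as a scoring system: no single measure, visit or contrast is fixed, and error is not controlled across its three measures

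*Protocol article*

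**What the plan says.** The section Primary Outcome (Neurological) of the protocol article opens with "The primary outcome will measure the severity of injury with the ASIA Scoring System" and then describes three measures:

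- the AIS grade, ordinal from A to E;
- the motor score, for which "A total possible score of 50 for the upper extremities and 50 for the lower extremities may be obtained", with key muscles from both arms and legs ("eg, elbow flexors, wrist extensors, hip flexors, quadriceps, and dorsi flexors");
- the sensory score: "Scores are summed to give a total possible score of 224".

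None of the three is singled out. Patient Recruitment and Parameter Recording sets assessments after the intervention and at 1, 2 and 3 months, and marks none as primary. Experimental Groups, Mode of Stimulation and Site of Stimulation set up five arms and two sets of comparisons (groups 1 to 3 by mode, groups 3 to 5 by site) without ranking them.

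Statistical Analysis plans repeated measures ANOVA or, for skewed data, the Friedman test. Categorical variables go to chi-square or Fisher tests. Post hoc pairwise comparisons get a Bonferroni or Tukey correction. A general sentence refers to multiplicity corrections as specified, but none is specified across the three ASIA measures. The significance rule is that a P "value less than .05 with a 95% CI will be considered statistically significant".

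Eligibility is limited to a "thoracolumbar (T1-L5) SCI and complete motor loss below the lesion level".

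**The concern.** A confirmatory trial needs one question whose answer is fixed in advance. Here the AIS grade, the motor score or the sensory score could each be reported as the primary result, at any of several visits and for any of several contrasts, without departing from the text. Each extra route to a positive finding at .05 raises the chance of at least one false one.

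This goes beyond detail that an article may leave to an analysis plan. The article does state its primary outcome, but in a form that does not identify the variable.

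A second, separate issue is targeting. Study Objectives puts motor recovery first, and Intervention Protocol aims the cortical stimulation at the leg area. Yet half of the points in the motor total belong to the arms, which lie above most of the eligible lesions.

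**Working it through.** **The plan's own figure.** The article gives no error rate for the primary outcome. Its only related figure is the sample size of 6, then 8 per group, then 40. With a difference of 13.53 − 12.85 = 0.68, SD 0.3 and two-sided α .05, t-test power is 87.9% at 5 per group and 94.2% at 6, so 6 is right for 90%. Then 6 / (1 − 0.20) = 7.5, rounded up to 8, and 8 × 5 = 40. The arithmetic is sound. It rests on MEP amplitude, however, so it does not show which ASIA measure was meant.

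**Can one test cover all three measures?** Not under the stated plan. The motor and sensory scores go to repeated measures ANOVA (or Friedman), and the AIS grade, if treated as categorical, goes to chi-square or Fisher. That makes at least three separate analyses at .05.

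**Three measures, one test each.** With k independent tests, the chance of at least one false positive is 1 − (1 − .05)^k.

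- k = 3: 1 − 0.95³ = 0.143, or 14.3%.
- The three measures are likely to be positively correlated. The documents give no correlations, so a range is assumed. With 200,000 simulated sets of normal test statistics, the rate is 13.6% at a correlation of 0.3 and 9.8% at 0.8. The range is therefore about 10% to 14%.

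**Three measures at four visits, all tested separately.**

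- k = 3 × 4 = 12: 1 − 0.95¹² = 0.460, or 46.0%.
- With assumed correlations of 0 to 0.8 between measures and 0.5 to 0.9 between visits, the rate is about 17% to 40%.

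For the motor and sensory scores, one repeated measures model can take in all visits, so the 12-test count overstates what the plan implies. Chi-square and Fisher tests have no visit dimension, so the visit for the AIS grade stays open.

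**If all tests were kept under Bonferroni.** The thresholds would be .05 / 3 = .0167 or .05 / 12 = .0042. On the protocol's MEP inputs, with 6 completers per group, power would fall from 94% to 83% or 60%. No ASIA effect size or SD is given, so power for the primary outcome itself cannot be computed.

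**Motor total.** 10 muscles × 2 sides × 5 points = 100, of which 50 / 100 = 50% are upper-extremity. For lesions clearly below the arm segments these points should sit at or near their ceiling. That is an inference from the lesion level, because the article does not report arm scores or map muscles to segments.

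**The case against.** The other side has several good points.

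- **Some control exists.** Repeated measures ANOVA can handle the visits for the two scores, and nothing restricts the pairwise correction to pairs of groups. This stands, and it makes 46% a worst case rather than the plan's error rate.
- **The arm points do not cause the multiplicity.** A reader might infer that a half-fixed motor total is why there is no single test. It is not: the gap comes from the unnamed measure, visit and contrast. Nor do constant points add noise. They drop out of change from baseline and leave group differences as they are. What remains is poor targeting of the scale.
- **Cannot change is too strong.** The documents do not say so, and it is least safe at T1, where a hand muscle may be affected.
- **AIS conversion is not shown to be useless.** One might argue that Fisher's test on 8 v 8 needs 7/8 v 0/8 to pass P < .005. That threshold assumes all 10 pairs of arms. The protocol sets two families of three, so 6 pairs and .05 / 6 = .0083, which 6/8 v 0/8 (P = .007) already passes. Collapsing an ordinal grade into two categories also discards information.
- **Sensory recovery is an aim too.** The abstract's objective names motor and sensory function together. Ranking motor first follows Study Objectives but is still a choice for the sponsor.
- **A fuller document may settle it.** An analysis plan or registry entry, neither of which is shown, may rank the measures. If so, the article should carry that ranking.

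None of this supplies a primary measure, visit or contrast, or any control across the three measures.

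**Conclusion.** The concern holds in a limited form. The primary outcome is three measures, with no primary component, visit or contrast among five arms and no error control across components. The supportable size is a family-wise error of up to 14.3%, or about 10% to 14% for assumed correlations of 0.8 to 0.3. This takes one test per measure at .05 and leaves aside the choice of visit and contrast. Separate testing at every visit would put the ceiling at 46%, which the plan does not require.

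The motor total is a separate and lesser matter. Half of its points have little room to change in most eligible patients, so it describes recovery below the lesion poorly. It neither inflates the error rate nor, on change scores, adds much variance. The sponsor should correct the definition; the stated sample-size arithmetic is not in question here.

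**What to change.** Before unblinding, in a dated amendment that records that the choice was made blind to allocation, name:

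1. one primary ASIA variable, for example the lower-extremity motor score (0 to 50), adjusted for baseline because eligibility runs to L5 and some lumbar lesions spare leg muscles;
2. one visit, for example 3 months;
3. one contrast, or an ordered set of contrasts, among the five arms. A between-group difference alone would not be enough, because it still leaves the deciding pair open.

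Make AIS conversion, the sensory scores and the other visits secondary, either labelled supportive or tested in a fixed order after the primary.

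No new measurement is needed, since the lower-extremity score is already part of the examination. The costs are the amendment, a registry update and the loss of primary status for the sensory and AIS results. Timing matters: the article dates the start to January 2023 and the analysis to January to July 2025, so a choice without a recorded date and blinding status could be read as made after seeing the data.

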#### Secondary Outcomes

##### Functional Parameter Outcomes

Walking Index for Spinal Cord Injury II (WISCI-II) is a 0-20 level scale that evaluates the walking activity of a patient based on physical assistance, the need for braces and walker, and other adaptive devices. The levels on the scale are scored from 0 (patient unable to walk) to 20 (patient walking without braces and adaptive devices and without any physical assistance for at least 10 m) [12].

Spinal Cord Independence Measure-III (SCIM-III) includes 19 tasks organized in 3 subclasses based on the patient’s general activity: self-care (score 0-20), respiration and sphincter management (score 0-40), and mobility (score 0-40). The overall scores range from 0 to 100, where a 0 score defines a total dependence of the patient on the caregiver and a score of 100 indicates complete independence [13].

##### Electrophysiological Parameter Outcomes

###### Single-Pulse TMS

A single pulse of TMS at minimum stimulus intensity will be delivered at the motor cortex that elicits an MEP of ≥ 50 µV at least 5 out of 10 trials in the target muscle (APB) and will be recorded as RMT [14]. For recording the inhibitory activity, a single TMS is delivered to produce an interruption in ongoing EMG activity during a tonic contraction followed by the reoccurring EMG activity. The duration of silencing of EMG in response to TMS will be measured as a cortical silent period (cSP) [15]. The recruitment curve plotted between the TMS intensity (%) and MEP sizes.

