**Objective:**

This study aims to assess the effect of iTBS on corticospinal tract integrity, plasticity, and regaining of motor and sensory function in patients with cSCI. The rationale behind using an iTBS protocol is to modify and augment the communication between spared neurons of the corticospinal tract and strengthen the synaptic transmission, which will improve motor function in underlying muscles.

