In addition, SC stimulation can modulate the activity of the local central pattern motor generators, which promotes synaptic strengthening [28]. In rat models of complete and incomplete SCI, a significant attenuation of glial scaring, lesion volume, neurotransmitter imbalance, muscle atrophy, and facilitation of neuronal survival, axonal regeneration, and myogenesis has been shown following whole-body magnetic field exposure [29,30]. Therefore, we propose that SC stimulation along with motor cortical stimulation would attenuate secondary damage and promote regeneration even in patients with cSCI, leading to long-term functional recovery.

Various single- and paired-pulse paradigms of TMS have been used for the assessment of cortical excitability, plasticity, integrity of the corticospinal tract, and excitatory-inhibitory neural circuitry of the motor cortex. We shall use all paired-pulse paradigms (short-interval intracortical inhibition, intracortical facilitation, and long-interval intracortical inhibition) to objectively assess excitatory-inhibitory neural circuitry and single-pulse paradigms (RMT, MEP, recruitment curves, and contralateral silent period) for unraveling the excitability of corticospinal circuitry and motor units.

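### TMS recordings from a hand muscle that is never below the lesion cannot show corticospinal tract integrity across a T1-L5 injury, although tract integrity is a stated aim

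*Protocol article*

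**What the plan says.** **Aim.** The Abstract (Objective) states: "This study aims to assess the effect of iTBS on corticospinal tract integrity, plasticity, and regaining of motor and sensory function in patients with cSCI". Findings on corticospinal excitability are expected in the Abstract (Results). In the Discussion (Principal Findings), TMS paradigms are said to "have been used for the assessment of cortical excitability, plasticity, integrity of the corticospinal tract". That section then commits this trial to the paired-pulse measures for intracortical circuitry, and to RMT, MEP, recruitment curves and the silent period for corticospinal excitability.

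**Population.** Inclusion and Exclusion Criteria admit adults "with a thoracolumbar (T1-L5) SCI and complete motor loss below the lesion level", graded ASIA A.

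**Recording site.** Under Single-Pulse TMS, the threshold is the intensity that elicits a response "in the target muscle (APB) and will be recorded as RMT". The Intervention Protocol names the same site: "RMT will be recorded by placing figure-eight coils over the motor hotspots of the APB". No other muscle is named for a TMS recording. The silent period is measured during a tonic contraction, with no muscle given. Paired-Pulse TMS names no muscle either.

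**Treated site.** Cortical treatment is aimed at the leg area of the motor cortex. Spinal treatment is given over the injury site.

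**The concern.** An MEP tests the pathway only as far as the muscle it is recorded from. If that muscle is supplied from cord at or above the injury, the response can be normal when nothing passes through the lesion. It can also change with no change in conduction through the lesion.

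Two wrong conclusions are then possible. A rise in hand MEPs could be reported as corticospinal recovery after complete injury, or a flat result as failure to restore the tract. The recordings would support neither. Treatment and readout also address different cortical representations: leg area or cord for treatment, hand area for recording.

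**Working it through.** This is a question of what is measured, so the check sets the sections side by side.

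1. **Is the recording muscle fixed or left open?** Fixed for RMT. Both Single-Pulse TMS and the Intervention Protocol name APB, and the former calls it the target muscle.

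2. **Where does APB lie relative to the lesion?** The article gives no segmental level. Assumption from general anatomy: APB is supplied from about C8-T1.
   - Lesions from T2 to L5: APB is above the lesion.
   - Lesions at T1: the injury may involve APB's own segment, so APB is at the margin, and an intact pathway cannot be taken for granted.
   - In no eligible patient is APB below the lesion. The result is the same whether C8 or T1 dominates.

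3. **Which measures are affected?**
   - RMT: explicit in the text.
   - Cortical silent period: strong inference. It needs a voluntary contraction, and patients with complete motor loss cannot make one below the lesion.
   - Recruitment curve and the paired-pulse measures (short- and long-interval inhibition, facilitation): weaker inference. APB is the only target muscle given, but the text does not tie it to these.

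4. **What can the measures show?** Cortical excitability, intracortical inhibition and facilitation, and excitability of the corticospinal path down to the hand segments. Conduction across a T1-L5 injury is outside their reach.

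5. **Does the planned sample size bear on this?** Inputs from Sample Size: means 12.85 and 13.53 (difference 0.68), SD 0.3, two-sided alpha 0.05, power 0.90.
   - Normal approximation: n = 2 × [0.3 × (1.960 + 1.282) / 0.68]² = 4.09, so 5 per group.
   - Exact t test: power 0.879 with 5 per group and 0.942 with 6, so 6 per group.
   - Dropout: 6 / 0.8 = 7.5, so 8 per group; 8 × 5 = 40.
   - The stated 6, 8 and 40 reproduce. The arithmetic stands and does not depend on this point.

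6. **What could a leg recording show with 8 per group?** For MEP presence or absence, two groups, two-sided Fisher test, no dropout and no multiplicity correction:
   - 4/8 against 0/8: 2 × C(8,4)/C(16,4) = 2 × 70/1820 = 0.077.
   - 5/8 against 0/8: 2 × C(8,5)/C(16,5) = 2 × 56/4368 = 0.026.
   - At least 5 of 8 would have to regain a response, against none, to fall below .05. Such an outcome can only be exploratory.

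**The case against.** The strongest reply is that tract integrity carries little weight in the article. Study Objectives lists cortical excitability and neuroplasticity, not integrity. The Discussion mentions integrity only in a general sentence on past uses of TMS, and its commitment for this trial is narrower. APB is also a defensible site for threshold, recruitment-curve and paired-pulse measures, because these need a response that can be elicited, and many leg responses will be absent in ASIA A patients. The full protocol may name leg recordings.

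Much of this stands. APB is a sound site for the excitability aims, and the clear conflict lies mainly in the Abstract's Objective. But that sentence is a stated aim, and the article names no other electrophysiological route to it. Nor is the site merely unstated: the article fixes one, and that one does not fit the aim.

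Some stronger readings are tempting but not supported:
- *APB lies above every eligible lesion and is always intact.* Not established at T1.
- *No MEP measure, as described, crosses the injury.* The muscle is explicit only for RMT.
- *The trial was sized on a measure that misses the question.* Sample Size does not name the muscle behind its MEP figures, and the cited study is not at hand.
- *The Objective claims tract integrity in the muscles below the lesion.* It claims improved motor function there, which the primary ASIA motor score and WISCI-II address.
- *The conclusions overstate integrity.* Neither the Abstract's conclusion nor the final one mentions tract integrity.

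**Conclusion.** The concern holds as a mismatch between one stated aim and the only recording site named. In all 40 planned patients APB lies above the lesion or, for T1 injuries, at its margin. The TMS measures recorded there cannot show corticospinal tract integrity or conduction through the injury. They remain valid for cortical and supralesional excitability and for intracortical circuitry.

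The reach is limited. Electrophysiology is a secondary outcome, and the primary ASIA outcome and the sample-size arithmetic are not touched. The verdict rests on two assumptions: APB supply at about C8-T1, and APB as the site for the MEP measures with no named muscle. If the full protocol names a muscle below the lesion for any of them, the point falls for those measures and the article should say so. The use of the APB threshold to set stimulation intensity is a matter of treatment delivery, on which this point takes no position.

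**What to change.** **Wording (recommended, feasible at any time before reporting).** In the Abstract's Objective, replace tract integrity with supralesional corticospinal and cortical excitability. Read the corresponding statements in the Abstract's Results and in Principal Findings in the same sense. State that changes in APB measures will not be interpreted as tract integrity or as recovery through the lesion. Name the recording muscle for each TMS measure. Cost: text only.

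**Optional recording.** Where TMS visits remain, also record from a lower-limb muscle below the lesion and report MEP presence or absence as an exploratory integrity outcome. Cost: an extra electrode site and a few minutes per visit. Downsides: the project started in January 2023 with completion expected in mid-2025, so leg baselines cannot be recovered for patients already treated; many responses will be absent; and power is low with 8 per group.
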